### Interim analyses {21b}

N/A. We do not have a planned interim analysis for this study.

### Methods for additional analyses (e.g., subgroup analyses) {20b}

We will perform sensitivity analyses to evaluate the relationship between sex and the primary outcome measures. No additional analyses are planned.

### Methods in analysis to handle protocol non-adherence and any statistical methods to handle missing data {20c}

In the case(s) where a participant drops out of the study after receiving their first dose of placebo/psilocybin then the last observation/data will be included in an intention-to-treat analysis.

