**Methods:**

Fifty participants diagnosed with MDD or persistent depressive disorder (PDD) will be recruited from a tertiary mood disorders clinic and undergo 1:1 randomization into either an experimental or control arm. Participants will be given either 25 mg psilocybin or 25 mg microcrystalline cellulose (MCC) placebo for the first treatment. Three weeks later, those in the control arm will transition to receiving 25 mg psilocybin. We will investigate whether treatments are associated with changes in arterial spin labelling and blood oxygenation level-dependent contrast neuroimaging assessments at acute and subacute timepoints. Primary outcomes include testing whether psilocybin demonstrates acute changes in (1) cerebral blood flow and (2) functional brain activity in networks associated with mood regulation and depression when compared to placebo, along with changes in MADRS score over time compared to placebo. Secondary outcomes include changes across complementary clinical psychiatric, cognitive, and functional scales from baseline to final follow-up. Serum peripheral neurotrophic and inflammatory biomarkers will be collected at baseline and follow-up to examine relationships with clinical response, and neuroimaging measures.

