The neurobiological mechanisms underpinning psilocybin’s antidepressant response remain unclear but likely involve changes in neuroplasticity at both cellular [36, 37] and connectomic level [37–39]. In this context, *neuroplasticity* refers to the brain’s ability to adapt structurally and functionally in response to psilocybin [40–42]. Previous research in MDD suggests increased dynamic functional activity and neural flexibility measured by BOLD-fMRI and magnetic resonance spectroscopy [43] during the subacute treatment phase (days to weeks post-dosing). However, the acute effects (e.g., < 24 h post-dosing) of psilocybin-evoked neuroplasticity in MDD remain unknown. Moreover, psilocybin’s agonism at serotonin 5-hydroxytryptamine (5-HT) receptors and its role as a glutamatergic agent are implicated in its neuroplastic mechanisms [44–47] and psychological phenomena such as ego dissolution (i.e., the subjective experience of a breakdown in one’s sense of self and separation between oneself and the world) [43, 48, 49], dream state-like cognitive processing [12, 49], and putative molecular antidepressant mechanisms [36, 50–52].

Placebo effects are well-documented in conventional antidepressant trials in the absence of acute treatment effects [53, 54]. Spontaneous remission of untreated MDD symptoms can occur for many reasons but may take longer compared to antidepressant treatments [55–57]. A recent phase 2 trial comparing psilocybin to an active placebo alongside supportive psychotherapy found significant benefits of psilocybin over placebo on Montgomery-Åsberg Depression Rating Scale (MADRS) and Sheehan Disability Score measures up to 6 weeks post-treatment [58]. However, no difference in MADRS was found at 2 days post-treatment, suggesting psilocybin’s neurobiological effects occur before symptom improvement. This underscores the need to investigate acute brain network changes during psilocybin treatment versus placebo to better understand how psilocybin immediately alters functional connectivity and the neurophysiological mechanisms linked to mood changes in MDD. This exploration may aid in identifying early treatment response markers [54]. For this study, the “acute” timeline will denote any changes that manifest on the day of psilocybin treatment, whereas the “subacute” timeline will encompass any change that occur during the subsequent weeks of follow-up.

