### Criteria for discontinuing or modifying allocated interventions {11b}

According to the terms of participant safety and voluntary withdrawal, participants who request withdrawal from the study at any time will be immediately withdrawn with no further data collected and the cessation of intervention administration. Participants will not be required to provide reasoning for their withdrawal of consent. However, if reasoning for study withdrawal is voluntarily provided, this will be recorded along with survival data up to the protocol-described follow-up period. Any data collected prior to the withdrawal of consent may be retained and used by Sunnybrook Research Institute. Research staff may also withdraw participants if they are rendered unable to tolerate the trial medication, whether there is a serious adverse event or a persistent adverse event that impedes their daily functioning. The withdrawal procedure also extends to those who are unable or unwilling to follow the study procedures, those who are diagnosed with any medical condition that, in the Qualified Investigators’ opinion, may jeopardize their safety if they were to continue in the trial. If the participant plans to or becomes pregnant during the trial, the QI may stop a participant’s involvement in the study without their consent. If the Sponsor decides to stop the study or if the Regulatory Authority(ies)/research ethics board withdraws permission for the study to continue, the immediate cessation of involvement for all participants will be done without their consent.

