### Composition of the data monitoring committee, its role and reporting structure {21a}

For this trial, two psychiatrists at Sunnybrook Health Sciences Centre who are not directly involved with the study, with no financial relationship with the study, will serve as independent medical monitors (IMMs) for the study. The IMMs will have relevant expertise with psychopharmacology and will have the primary responsibility to provide independent safety monitoring in a timely fashion. This will be accomplished by reviewing adverse events, immediately after they occur or are reported, with follow-up through resolution. During the trial, the monitors will evaluate individual and cumulative participant data and provide recommendations regarding the safe continuation of the study.

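### Read as carry-forward, the dropout rule enters placebo-phase MADRS scores as control-arm week-6 results and tilts that comparison towards early psilocybin

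*Protocol article*

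**What the plan says.** Section {20c} of the protocol article is the only place that deals with missing data. It begins "In the case(s) where a participant drops out of the study after receiving their first dose of placebo/psilocybin" and concludes that "the last observation/data will be included in an intention-to-treat analysis". Section {20b} limits sensitivity analyses to sex and plans no others.

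Table 2 lists MADRS change to week 3 and to week 6 after the first administration as a primary outcome, and remission at the same two times as a secondary one. Section {20a} plans mixed-effects linear regression for both CBF and MADRS. On the delayed start, the abstract says: "Three weeks later, those in the control arm will transition to receiving 25 mg psilocybin". Group 1 also receives psilocybin at that visit.

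Section {11b} says that participants who request withdrawal are "immediately withdrawn with no further data collected and the cessation of intervention administration". It allows staff to withdraw participants for intolerance or adverse events, and then adds: "The withdrawal procedure also extends to those who are unable or unwilling to follow the study procedures". Section {21a} has the independent medical monitors "reviewing adverse events, immediately after they occur or are reported, with follow-up through resolution".

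**The concern.** Carry-forward assumes that a participant's last score would have stayed the same. In this design, a control participant who leaves before Treatment Visit 2 has only placebo-phase scores, and one of them would be entered for a visit at which the arm is meant to have had psilocybin. A group 1 participant who leaves at the same time has a score carried from after a psilocybin dose, so the error differs between arms.

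The result would make the control arm look worse at week 6, understate its change after psilocybin, and overstate the advantage of starting early. Week-6 remission inherits the error. The carried values would also be treated as if they had been observed. Because {20b} plans no other sensitivity analysis, nothing in the article would show the problem.

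**Working it through.** **The plan's own figure.** The only power calculation is for CBF: 20 per group for more than 80% power. Simulating from the stated inputs (baseline 55, SD 13; psilocybin effect 23%, SD 23%; retest variability 3%) gives power at 20 per group of:

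- 0.98 with two visits and no Sidak correction
- 0.95 with two visits and Sidak for three contrasts
- 0.91 with three visits and no correction
- 0.77 with three visits and Sidak

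The claim is met in three of four variants. The calculation as described has no dropout and does not cover MADRS, so it does not bear on week 6.

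**Primary CBF contrast.** The visit-1 scan is about one hour after dosing, so anyone who leaves later already has both values. With 25 per arm, the simulated contrast is 12.69 mL/100 g/min without dropout (expected 0.23 × 55 = 12.65) and 12.63 with 20% leaving after that scan and the value carried. Power is 0.90 and 0.92 respectively. Only leaving between dose and scan matters. With baseline carried, 10% gives 11.39 (0.90 × 12.65 = 11.39) and 20% gives 10.1 (0.80 × 12.65 = 10.12).

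**Week-6 MADRS.** Let d_P and d_C be the fractions leaving before Treatment Visit 2, and g_P and g_C the further improvement from week 3 to week 6 in each arm. A negative difference favours psilocybin first. If dropout is completely random and the week-3 score is carried:

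bias = d_P × g_P − d_C × g_C

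With equal dropout d, this is −d × (g_C − g_P), which is not zero unless the two further improvements are equal.

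Assumed values, none from the article: mean change in the psilocybin arm −12 at week 3 and −13 at week 6 (g_P = 1); in the control arm −5 and −13 (g_C = 8). The true week-6 difference is then 0. The simulation used SD 8, correlation 0.6, 25 per arm, 3,000 replicates, a two-sample t-test at week 6, and dropout more likely after a poor week-3 score.

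| Dropout, psilocybin / control | Formula | Simulated, carried forward | Rejection rate, carried forward | Rejection rate, complete data |
|---|---|---|---|---|
| 5% / 5% | 0.05 − 0.40 = −0.35 | −0.41 | 5.4% | 4.7% |
| 10% / 10% | 0.10 − 0.80 = −0.70 | −0.76 | 5.7% | 5.6% |
| 20% / 20% | 0.20 − 1.60 = −1.40 | −1.36 | 7.9% | 5.0% |
| 5% / 20% | 0.05 − 1.60 = −1.55 | −1.78 | 9.3% | 5.0% |
| 10% / 30% | 0.10 − 2.40 = −2.30 | −2.64 | 15.9% | 5.3% |

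Simulation error is about 8 × √(2/25) / √3000 = 0.04 points for the bias and √(0.05 × 0.95 / 3000) = 0.4 percentage points for the rejection rate. The bias is therefore clear in every row. The excess in type I error is clear only in the last three.

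A likelihood estimate from the observed visits, without carry-forward, stays within 0.1 point of zero in all five rows.

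**Week-3 MADRS.** Assume day-1 mean changes of −10 (psilocybin) and −4 (control), carried to week 3 values of −12 and −5. The bias is 2 × d_P − 1 × d_C. It runs from −0.3 (0% / 30%) to 0.4 − 0.2 = +0.2 (20% / 20%).

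**The case against.** The strongest reply is about wording. The article does not use the term carried forward. Section {11b} lets data collected before withdrawal be kept and used, and a mixed model needs no imputation. The sentence could mean only that dropouts' collected data stay in the analysis, which would be harmless. This stands as a possible reading. But the sentence speaks of the last observation, under a heading on handling missing data, so carry-forward is the more natural one, and the sentence needs rewording either way.

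A reader might infer that every contrast is biased. The documents do not support that: the powered CBF contrast is essentially untouched, and week 3, the placebo-controlled MADRS comparison, moves by a few tenths of a point at most on the assumed values. The background remark that "no difference in MADRS was found at 2 days post-treatment" adds little. It reports another trial with an active placebo, and which scales are collected on day 1 and at week 1 cannot be confirmed because the schedule figure is not shown.

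A reader might also infer that {11b} ends data collection after adverse-event withdrawals and so contradicts {21a}. The phrase on collecting no further data is attached to participants who request withdrawal. How far it reaches staff-initiated withdrawals is unclear, and safety follow-up can continue after outcome collection stops. This is an ambiguity, not a proven conflict.

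Finally, at week 6 both arms have had psilocybin, so the affected comparison has no concurrent placebo. That limits the damage, but week-6 MADRS is still listed as primary.

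**Conclusion.** The point holds for week-6 MADRS and the remission outcome derived from it, if {20c} means carry-forward. On the assumed trajectories the bias favours early psilocybin by about 0.4 points at 5% dropout per arm, 0.8 at 10%, 1.4 at 20%, and 2.6 at 10% / 30%. Type I error is close to nominal at 10% per arm or below and reaches about 16% in the most unequal case.

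The direction rests on controls improving more between weeks 3 and 6 than group 1, whose second visit is a repeat dose. That follows if psilocybin works and a second dose adds less than a first. With g_P = 1 and g_C = 8, psilocybin-arm dropout would have to exceed eight times control-arm dropout to reverse it. The size depends on dropout rates and trajectories that the article does not give.

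No claim is made against the primary CBF contrast, and none of consequence against week-3 MADRS.

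**What to change.** Replace the sentence in {20c} with a statement that all observed visits are analysed by randomised arm in the likelihood-based mixed model already planned in {20a}, that no values are carried forward, and that a sensitivity analysis will examine informative dropout. Its detail can be left to the analysis plan. If the sponsor meant only that data collected before dropout are kept, the sentence should say that.

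Separately, clarify in {11b} whether the end of data collection applies to staff-initiated withdrawals as well as to participants' own requests, and reconcile the answer with the adverse-event follow-up in {21a}.

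The cost is a few sentences and an amendment submitted to the research ethics board as {25} describes. Replacing the rule needs no new visits or data. The small statistical price is reliance on missing at random, which the sensitivity analysis is there to test.

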### Plans to give access to the full protocol, participant-level data, and statistical code {31c}

Once the primary and secondary a priori endpoint data has been reported, we intend to share our data upon written request with qualified investigators. Data sharing agreements will be in place.

## Oversight and monitoring

### Composition of the coordinating center and trial steering committee {5d}

As this is an investigator-initiated, single-center study, the Trial Steering Committee will be composed of the study’s principal investigators, [name] ([name]) and [name] ([name]) who will meet once a month to review the study’s progression, its safety data, and ensure adherence to ethical and regulatory standards. The study coordinator will act as the coordinating center for this study, ensuring daily management of the trial that includes appropriate data management, maintaining the blind, safety reporting, statistical analysis of data, communication between the study team and regulatory authorities, and regulatory compliance. The daily activities required for the study will be carried out by the QI, study coordinator, study psychotherapist, and research assistants, who will also meet weekly to discuss study progression.

### Composition of the data monitoring committee, its role and reporting structure {21a}

For this trial, two psychiatrists at Sunnybrook Health Sciences Centre who are not directly involved with the study, with no financial relationship with the study, will serve as independent medical monitors (IMMs) for the study. The IMMs will have relevant expertise with psychopharmacology and will have the primary responsibility to provide independent safety monitoring in a timely fashion. This will be accomplished by reviewing adverse events, immediately after they occur or are reported, with follow-up through resolution. During the trial, the monitors will evaluate individual and cumulative participant data and provide recommendations regarding the safe continuation of the study.

### Adverse event reporting and harms {22}

Reporting of adverse events, including adverse drug reactions, will be recorded in the case report form/electronic case report form to be reviewed by the QI. If any AEs are deemed serious adverse events (SAEs) or serious unexpected adverse drug reactions (SUADRs), they will be recorded and promptly reported to the Sunnybrook REB and Health Canada in accordance with Division 5 of the *Food and Drug Regulations* and local reporting requirements and timelines.

### Frequency and plans for auditing trial conduct {23}

All study-related source data/documents will be made directly available to the IMMs and regulatory authorities including Health Canada and Sunnybrook REB when a formal audit, regulatory inspection, and/or trial-related monitoring is performed. All data that is collected will be accurate and verifiable by source documents using a clinical data management standard operating procedure. Quality assurance and control systems will be in accordance with ICH-GCP and local regulations.

### Plans for communicating important protocol amendments to relevant parties (e.g., trial participants, ethical committees) {25}

For any protocol amendments, study investigators will be notified of any changes made after mutual agreement of the proposed changes have been established across investigators. The Sunnybrook REB will be notified through the submission of a request form for protocol amendments. For any amendments that may affect participants involved in the study, these changes will be communicated to each participant once they have been made, to which we will look to obtain an updated informed consent. A completely new REB submission will be made for any substantial changes to the protocol.

### Dissemination plans {31a}

The results and experiences of this trial will be jointly published by the investigators in peer-reviewed medical and scientific journals. Ad hoc writing and publication committees will be defined for writing and reviewing publications. The support of the sponsor will be recognized in all publications that result from this study.

## Discussion

The EMBRACE trial will be the first to examine the real-time and subacute neuroplastic effects of high-dose synthetic psilocybin (25 mg) versus placebo in MDD using CBF and fMRI. Employing a non-psychoactive placebo and a delayed-start design, the study conducts serial MR with ASL perfusion-MRI and BOLD-fMRI sequences at baseline and 1-h post-dosing for each treatment visit. It aims to compare acute (intraday) CBF changes, psilocybin verses placebo response, subacute network changes, and cumulative treatment effects. While landmark clinical studies have demonstrated promising response rates with assisted psychotherapy, important drug mechanistic studies are lagging the enduring enthusiasm and emerging usage among the public [111].

Our protocol innovates several key aspects. Firstly, to our knowledge, only a few studies have integrated the combination of ASL perfusion and resting-state fMRI into their study design to examine CBF differences within healthy [33, 112] and treatment-resistant depression [113] populations. To address these gaps, this trial uses BOLD-ASL fMRI at three time points to acutely and sub-acutely capture the robust CBF hemodynamic responses to psilocybin in comparison to placebo in MDD. Secondly, a relatively high dose (25 mg) of psilocybin was chosen based on prior efficacy in depression and safety profiles [21, 114, 115]. Thirdly, the trial includes a tailored tapering period for conventional antidepressants to maximize participant safety and accurately characterize psilocybin-evoked brain activity. Additionally, this trial incorporates a comprehensive battery of clinical measures, including serial MADRS assessments, pre- and post-treatment, as well as follow-up time points to establish treatment efficacy, durability of clinical response, and exploratory relationships with neuroimaging measures. The brain-behaviour relationship as exhibited by both CBF alterations and MADRS scores will also be examined in this trial, including our blood biomarkers of interest that will complement the BOLD/ASL fMRI data.

Upon completion of the proposed study, our findings aim to establish psilocybin’s efficacy as a novel antidepressant therapy while elucidating its effect on brain networks associated with depression. Our hope is that the proposed study aims to inform decision-making and future treatment protocols in addressing the high prevalence of MDD by understanding the relevant mechanisms by which psilocybin exerts its therapeutic effects, ultimately contributing to more efficient treatment delivery and scalability.

## Limitations of the trial design

Anticipated limitations of our trial design include its single-center design and modest sample size, potentially limiting generalizability. To enhance statistical power, we have incorporated three imaging time points to improve our ability to detect intra-subject changes and focused our primary neuroimaging analysis on a priori brain regions linked to MDD and psilocybin’s effects.

## Trial status

The protocol version 4.7 was approved on 10 October 2023 by the Sunnybrook Health Sciences Centre REB. Recruitment is expected to commence in August 2024, and is expected to be completed by August 2027.

## Data Availability

Once data entry is complete and publication is finalized, access to the final trial dataset with deidentified participant data will only be available to the study investigators and coordinator. Deidentified safety data will be provided to Usona Institute in accordance with a formal agreement.

## Abbreviations

5-HT: 5-Hydroxytryptamine
AE: Adverse event
ASL: Arterial spin labelling
BDNF: Brain-derived neurotrophic factor
BOLD: Blood oxygenation level-dependent
CBF: Cerebral blood flow
CRF/eCRF: Case report form/electronic case report form
CRP: C-Reactive Protein
CSSRS: Columbia Suicide Severity Rating Scale
DMN: Default Mode Network
DSM-5.0: Diagnostic and Statistical Manual of Mental Disorders 5.0
ECG: Electrocardiogram
fMRI: Functional magnetic resonance imaging
GCP: Good Clinical Practice
HAMD: Hamilton Rating Scale for Depression
ICF: Informed consent form
ICH: International Council for Harmonisation
IMM: Independent Medical Monitor
LSD: Lysergic acid diethylamide
MADRS: Montgomery-Åsberg Depression Rating Scale
MAOI: Monoamine oxidase inhibitor
MDD: Major depressive disorder
MDE: Major depressive episode
MINI: Mini International Neuropsychiatric Interview V-5.0.0
mPFC: Medial prefrontal cortex
MR/MRI: Magnetic resonance/magnetic resonance imaging
PCC: Posterior cingulate cortex
PDD: Persistent depressive disorder
PHIPA: Personal Health Information Protection Act
PI: Principal Investigator
PO: Per os/by mouth
QI: Qualified Investigator
QTc: Q-T corrected
REB: Research Ethics Board
S100B: S100 Calcium Binding Protein B
SAE: Serious adverse event
SHSC: Sunnybrook Health Sciences Centre
SNRI: Serotonin and norepinephrine reuptake inhibitor
SPO2: Oxygen saturation
SPSS: Statistical Package for the Social Sciences
SPIRIT: Standard Protocol Items—Recommendations for Interventional Trials
SSRI: Selective serotonin reuptake inhibitor
SUADR: Serious unexpected adverse drug reaction
TCA: Tricyclic antidepressants
USP: United States Pharmacopeia
